### 2.3. Meal Tolerance Test

A 2 h MTT will be performed before and after each intervention phase to assess glycemic and insulinemic responses, as well as subjective appetite. Prior to the MTT day, it will be requested that subjects not consume alcohol and do not perform intense exercise during 24 h. On test days, after 12 h fasting, subjects will be appointed to the research center at 7:00 a.m., and they will first complete a 100 mm visual analog scale (VAS) self-reported paper questionnaire (time point 0) to measure subjective appetite [18]. Then, an intravenous catheter will be inserted into the antecubital vein of each subject, and a fasting blood sample will be taken (time point 0) for biochemical determinations. After, subjects will be given a standardized breakfast that consists of a nutritional supplement (Simisure; Modern Strategies; Mexico) and a 22 g Kellogg’s Rice Krispies bar (Kellogg’s Company, Battle Creek, MI, USA). The breakfast’s nutritional distribution will be added up to a total of 210 kcal, 7 g from protein, 38.5 g from carbohydrates, and 3 g from lipids. Blood samples will be collected after this breakfast at 15, 30, 60, 90, and 120 min. Glucose and insulin concentrations will be determined in these blood samples, and the VAS questionnaire will be applied 5 min before each sampling. During the test period, subjects will stay at the research center and will be free to read, use electronic devices, watch television, or engage in conversation.

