## 3. Procedure

### 3.1. Ethical Aspects

Research will be conducted in accordance with the principles of the Declaration of Helsinki. The study protocol was approved on 22 April 2021 by the Ethics Committee of the Universidad Juárez Autónoma de Tabasco (UJAT) (No. 0724), and it was registered on 10 April 2021 at the Australian New Zealand Clinical Trials Registry (ACTRN12621001531808). This trial will take place at the División Académica de Ciencias de la Salud (DACS) at UJAT. Informed consent will be obtained from participants by trained research coordinators., who will explain the study’s aims, potential risks, and participants’ right to withdraw from the experiment at any time. Personal information from enrolled participants will be collected and stored confidentially. As part of the informed consent process, participants will be informed that the study protocol includes the collection of blood and fecal samples.

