### 3.6. Statistical Analysis

Sample size calculation was performed using NCSS and PASS v. 11.0 software. To detect a difference of 10% in the primary outcome variable (glycemic response AUC) and considering a power of 80% and a type 1 error of 5% in a crossover design, a sample size of 19 participants was calculated. However, to allow for a dropout rate of 20%, 24 participants will be considered. Four samples per participant will be analyzed: two baselines and two endpoints. The primary analysis will be performed using GraphPad Prism v. 7.0 and QIIME Software. The D’Agostino and Pearson tests will be used to determine Gaussian distributions. Differences in fasting biochemical markers will be assessed using a one-way analysis of variance (ANOVA) in combination with Tukey’s post hoc test. Time-course data will be analyzed by two-way repeated measures (RM) ANOVA to assess the effects of treatment, time, and the interaction of treatment and time. The intervention´s effect on GM community dissimilarity will be analyzed with permutational multivariate analysis of variance (PERMANOVA) on the Bray–Curtis distance and visualized with Principal Component Analysis (PCoA). ANOVA, or the Kruskal–Wallis test, will be used to compare alpha diversity using the Shannon index. The Firmicutes/Bacteroidetes ratio (F/B ratio) will be calculated from relative abundances. A *p*-value < 0.05 will be considered significant for all analyses.

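### Two-way RM ANOVA of the meal-test time courses discards any participant with a missed draw or only one period, and the 24-for-19 allowance does not cover missed draws

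*Protocol article*

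**What the plan says.** Section 3.6 names one method for the meal-test curves: "Time-course data will be analyzed by two-way repeated measures (RM) ANOVA to assess the effects of treatment, time, and the interaction of treatment and time". It gives GraphPad Prism 7.0 and QIIME as the software.

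The data feeding that analysis are described in three places:

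- Section 3.6, on visits: "Four samples per participant will be analyzed: two baselines and two endpoints".
- Section 2.3, on draws: a fasting sample at time 0, and then "Blood samples will be collected after this breakfast at 15, 30, 60, 90, and 120 min". That makes six draws per test.
- Section 3.2 places a meal test before and after each of the two phases.

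The plan expects incomplete participation. Section 3.1 tells participants of their "right to withdraw from the experiment at any time". Section 3.6 sizes the trial on the glucose AUC: "a sample size of 19 participants was calculated", and then "to allow for a dropout rate of 20%, 24 participants will be considered". The article states no rule for a partly observed curve.

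**The concern.** Classical two-way RM ANOVA with both factors within participant works on a full rectangle of data. A person with one empty cell cannot be used unless a value is imputed or another model is fitted. Two kinds of participant are therefore lost:

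- someone with complete Phase I data and no Phase II;
- someone who attends every visit but lacks one draw, for instance because a catheter failed.

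The second loss is the more wasteful, because nearly all of that person's data exist. The first matters mainly for validity. A completers-only comparison can mislead if the people who leave differ in their observed Phase I response. A likelihood-based model that keeps their data is valid under the weaker assumption that withdrawal depends only on what was observed.

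The glycemic and insulinemic responses are the primary outcome in the Introduction, and this ANOVA is the only named test that fits a meal-test curve. With about 19 people, losing two or three matters.

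**Working it through.** **Inputs from the protocol article.** Evaluable number 19, dropout 20%, enrolled number 24, power 80%, type 1 error 5% (section 3.6). Six draws per test (section 2.3). Four tests, two of them endpoints (sections 3.2 and 3.6).

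**Assumptions, not in the article.** Per-draw probability of a missed sample p = 0.5%, 1% or 2%, independent across draws. Within-person correlation 0.3 to 0.8.

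**Step 1. Reproduce the allowance.** 19 / (1 - 0.20) = 23.75, rounded up to 24. This matches the article. In reverse, 24 x 0.80 = 19.2 completers, so withdrawal at the planned rate is fully paid for and nothing is left over. The Abstract and section 2.1 give 23 participants instead of 24. At 23 the figure is 23 x 0.80 = 18.4, already below 19.

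**Step 2. Count the cells.** If only the two endpoint tests enter the model, a complete participant needs 2 x 6 = 12 draws. If all four tests enter one model, it is 4 x 6 = 24. The article does not say which.

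**Step 3. Share of participants with at least one missed draw,** 1 - (1 - p)^m, and complete cases left, 19.2 x (1 - p)^m:

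| p | m = 12: share lost | complete of 19.2 | m = 24: share lost | complete of 19.2 |
|---|---|---|---|---|
| 0.5% | 5.8% | 18.1 | 11.3% | 17.0 |
| 1% | 11.4% | 17.0 | 21.4% | 15.1 |
| 2% | 21.5% | 15.1 | 38.4% | 11.8 |

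**Step 4. Allow for clustering.** A failed catheter usually costs several draws at once. If draws are lost in threes at the same per-draw rate, the exponent becomes m/3. For 24 draws, 1 - (1 - p)^8 gives 3.9%, 7.7% and 14.9%. For 12 draws, 1 - (1 - p)^4 gives 2.0%, 3.9% and 7.8%. Step 3 is therefore the upper part of the range.

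**Step 5. What one-period participants are worth.** Take 19 completers (10 and 9 by sequence) and add five people with Phase I only, one endpoint value per phase, fitted by generalised least squares. The ratio of the completers-only standard error to the all-data standard error is 1.046, 1.033, 1.020 and 1.013 at within-person correlation 0.3, 0.5, 0.7 and 0.8. The gain in precision is thus 1% to 5%.

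**Step 6. Check the obvious replacement.** A mixed model with a participant random effect alone treats the six draws of one visit as independent given the person. In a simulation with 19 people, two visits, six draws and no treatment effect, its nominal 5% treatment test rejected about 12%, 25% and 35% of the time when visit-level variance was 10%, 30% and 50% of the within-person variance (assumed). A test on each participant's visit means stayed near 5%. The replacement model needs a visit-level term.

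**The case against.** The strongest reply is that the article does not say incomplete participants are deleted, and that rules for gaps usually sit in an analysis plan or full protocol that is not shown. Silence on missing data is indeed no defect here. But the article does not leave the method open. It fixes RM ANOVA, and any later rule would have to replace it or work around it.

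Three stronger readings are tempting, and the text does not support them.

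- **That planned withdrawal pulls the trial below its target.** It does not: 24 enrolled at 20% dropout leaves 19. Nor does the article say when dropout is expected, so it cannot be assumed to fall after Phase I. Losing one-period participants is largely inherent in a within-person comparison, and Step 5 shows how little precision they would return.
- **That the primary analysis loses these participants.** The powered variable is the glucose AUC, and the time-course ANOVA is not labelled primary. A trapezoidal AUC can still be formed when an intermediate draw is missing, so one missed draw need not remove anyone from an AUC comparison. The article names no separate test for the AUC, so the ANOVA's role is uncertain in either direction.
- **That power falls to a particular figure.** One could back-solve the effect that gives 80% power at n = 19 (a standardised paired difference of about 0.68) and read off about 75%, 69% and 57% at n = 17, 15 and 12. Those figures join deletion under a 24-cell ANOVA to a paired test on AUC. No analysis in the article has that power, and the missed-draw rates behind the sample sizes are assumed.

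It also stands that the 24-draw requirement applies only if all four tests enter one model, and that independence overstates the losses when draws are missed together.

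**Conclusion.** The concern holds in a limited form. The method fixed for the meal-test curves discards usable data from anyone with an unfilled cell, and the enrolment allowance covers withdrawal but not incomplete tests.

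Under independent missed draws at 0.5% to 2%, the loss is 6% to 22% of participants on 12 endpoint draws and 11% to 38% on 24. It falls to about 2% to 8% and 4% to 15% if draws are lost in threes. These are illustrations of scale, not forecasts, because the article gives no missed-draw rate. The conclusion also rests on treatment being entered as a within-participant factor, which the crossover design implies but section 3.6 does not spell out.

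For one-period participants the issue is validity, not precision. Keeping their data protects against withdrawal that depends on observed Phase I results, but not against withdrawal driven by unobserved ones. A better method is available at little cost, so the change should be made, although nothing here shows that the trial would fail without it.

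**What to change.** In section 3.6, replace two-way RM ANOVA for the time-course data with a linear mixed model fitted by REML to every available draw from all randomised participants, including Phase I data from those who leave later. Specify:

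- fixed effects for treatment, time, treatment-by-time, period and sequence;
- random effects for participant and for visit within participant, or an equivalent within-visit covariance;
- a small-sample degrees-of-freedom correction such as Kenward-Roger.

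The visit-level term is essential, for the reason shown in Step 6. The period term is needed because Phase-I-only participants would otherwise let a period difference leak into the treatment contrast. State which visits enter the model, and report the complete-case RM ANOVA as a sensitivity analysis.

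The cost is somewhat more modelling work and a statistics package that fits such models. No visits, samples or participants are added.

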### 3.2. Trial Design

This study is a crossover, randomized controlled trial (RCT) to determine the effect of daily intake of sucralose on glycemic response, subjective appetite, and GM in subjects with overweight or obesity. Participants will be invited to attend the laboratory for preliminary measurements and baseline data after providing written informed consent. Following this, they will be randomly allocated into one of two treatment groups to receive either sucralose or glucose (control) daily for four weeks, each phase separated by a four-week washout period. An MTT, subjective appetite assessment, and stool collection will be carried out before and after each intervention phase (four measurement points). A flow diagram of the study protocol is shown in Figure 1, and the participant timeline actions are presented in Table 1.

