### 3.3. Recruitment

Trial participants who are overweight and obese will be screened and recruited by researchers at the DACS of the UJAT from Villahermosa, Tabasco, Mexico. Moreover, information flyers via social media containing the details of the trial will be posted at respective institutions, hospitals, and other public places. The researchers will enroll patients by the inclusion and exclusion criteria. Patient recruitment started in September 2023. A computer-based online random number generator (www.random.org) will be used to allocate participants to the respective interventions, either sucralose or glucose. Randomized treatments will be supplied in sealed envelopes.

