### 3.5. Data Collection and Management

The research staff will interview subjects to gather demographic information and other baseline characteristics of the study group, including NNS consumption frequency, anthropometric measures, and medical history (comorbidities, medications, smoking). All participants will receive medical and nutritional sessions during and following the study. At no time will the participants be identified by the publications or presentations derived from this study, and each of the data provided will be handled with absolute confidentiality. Stool samples will be used exclusively for genetic analysis of the bacteria. The genetic information of the participants will not be studied or analyzed.

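### None of the models named for this two-period crossover has a period term, so a difference between phase I and phase II goes into the error or, with unequal sequences, into the treatment contrast

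*Protocol article*

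**What the plan says.** Section 3.2 describes a two-period crossover in which participants are allocated "to receive either sucralose or glucose (control) daily for four weeks, each phase separated by a four-week washout period". Section 3.6 gives the analysis models by name:

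- Time-course data: two-way repeated measures ANOVA "to assess the effects of treatment, time, and the interaction of treatment and time".
- Fasting markers: one-way ANOVA with Tukey's test, so a single factor.
- Shannon index: ANOVA or Kruskal–Wallis.
- Community dissimilarity: PERMANOVA on the Bray–Curtis distance.

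In the first model, time belongs to the time-course data, which Section 2.3 defines as samples from 0 to 120 minutes around the test breakfast. Neither period nor sequence is named as a factor anywhere in the article.

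Section 3.5 adds: "All participants will receive medical and nutritional sessions during and following the study". The Abstract and Section 2.1 recruit 23 participants, while Section 3.6 says that "to allow for a dropout rate of 20%, 24 participants will be considered".

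**The concern.** In a two-period crossover each participant's sucralose–glucose difference also contains the difference between the phases, with a sign set by the order received. A period term removes it. Without one there are two consequences. If the sequences are nearly equal in size, the period effect mostly cancels from the mean but stays in the spread of the differences, which widens the error and lowers power. If they are unequal, part of it is also added to the estimated treatment difference.

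A period effect is possible here. Corresponding visits in the two phases are eight weeks apart (four weeks of intervention plus four of washout), and participants receive dietary and medical counselling while the trial runs. Glycaemia, weight, appetite and microbiota could all move over that time. The trial is small, so it has little room to absorb extra error or a chance imbalance.

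**Working it through.** **Inputs from Section 3.6.** The target is a 10% difference in glycaemic AUC, "considering a power of 80% and a type 1 error of 5% in a crossover design, a sample size of 19 participants was calculated", with 20% dropout. Two-sided testing is assumed.

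**The plan's own figures.** 19/(1 − 0.20) = 23.75, rounded up to 24, which reproduces Section 3.6. 19 × 1.20 = 22.8, rounded up, gives the 23 of the Abstract and Section 2.1. The 19 itself cannot be reproduced, because no SD is given. Solving a two-sided noncentral-t test for 80% power at n = 19 and a 10% difference gives an SD of paired differences of about 14.7% of mean AUC (noncentrality 10/(14.7/√19) = 2.97). This SD is an assumption.

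**Model.** As a stand-in for the treatment contrast on AUC, take one sucralose-minus-glucose difference per participant:

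D = τ + sπ + e, with s = +1 or −1 by sequence and π the phase II minus phase I shift.

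Without a period term:

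- bias = π(n1 − n2)/n
- added variance = π²[1 − ((n1 − n2)/n)²]

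The size of π is not in the documents. Values of 5% and 10% of mean AUC are assumed for illustration.

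**Sequence sizes.** With 23 enrolled the best split is 12:11, and with 19 completers it is 10:9. With 24 enrolled, 12:12 is possible, but dropout can unbalance it. The share of π that becomes bias is 1/19 = 5% at 10:9, 5/19 = 26% at 12:7 and 7/19 = 37% at 13:6.

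**Simulation results, n = 19** (true difference 10% for power, 0 for type I error):

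| Split | π | Bias, no period term | Type I error, no period term | Power, no period term | Type I error, period fitted | Power, period fitted |
|---|---|---|---|---|---|---|
| 10:9 | 0 | 0 | 5% | 80–81% | 5% | 80% |
| 10:9 | 5% | 0.3 points | 4% | 79% | 5% | 80% |
| 10:9 | 10% | 0.5 points | 2% | 71% | 5% | 80% |
| 13:6 | 5% | 1.9 points | 7% | 90% | 5% | 74% |
| 13:6 | 10% | 3.7 points | 10% | 93% | 5% | 74% |

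By formula, the bias in the last row is 10 × 7/19 = 3.7 points, against a target difference of 10.

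**Direction.** The rows take π to act in the same direction as the treatment effect in the larger sequence. The 90% and 93% at 13:6 are therefore produced by bias and are no gain. With π reversed, the same simulation at 10:9 gives power of about 74% and 60% for the two effects. At an exact 12:12 split, where sign does not matter, power with all 24 completing falls from 89% to 87% and 78%.

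**Averaging over sequences.** If each of 19 sequences is an independent coin toss, type I error without a period term is about 5% at π = 0, 5% and 10%, and average power is 80%, 76% and 64%. A split of 13:6 or worse then has a probability of about 17%.

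**The case against.** Several stronger readings are tempting, and the documents do not support them.

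- **Any time trend leaks into the result.** Each phase has its own baseline and endpoint, and Section 1 defines the secondary outcomes as changes across an intervention. In a contrast of within-phase changes, a level shift between phases cancels. A steady linear trend cancels too, because both phases last four weeks. What remains is a trend that makes the two phase changes differ. This narrows the point but does not remove it: Section 3.6 does not tie that contrast to the primary AUC, and endpoint comparisons stay exposed.
- **Allocation is unblocked.** Section 3.3 says only that an online random number generator "will be used to allocate participants to the respective interventions, either sucralose or glucose". It is silent on blocking, and a condensed article may leave block size and ratio to the full protocol. The point does not need this reading.
- **Advice on sweeteners creates a trend.** Section 2.2 has low intake maintained throughout the experiment. A condition held constant is no evidence of drift. The counselling sessions make a trend possible, but their content and timing are not given.
- **The trial's type I error is inflated.** Under simple randomisation the bias averages to zero and the overall rate is about 5%. The 10% figure requires both a 13:6 split and an assumed 10% period effect. Near balance the omission makes the test conservative.

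It can also be said that an analysis plan might add period. But the article lists the factors of its main model and names a single-factor model for fasting markers. The criticism is of a model as stated, not of a detail left out.

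**Conclusion.** The point stands in a limited form. The models as written omit a standard crossover factor, and following them leaves any period effect on the analysed contrast in the error, in the estimate, or in both. Near balance the likely harm is lost power: about 1 point for a 5% period effect and 9 points for a 10% effect at 10:9, and more if the effect opposes the treatment difference. At a poor split the realised estimate is biased by |n1 − n2|/n of the period effect, which is 3.7 points at 13:6 with a 10% effect.

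These sizes rest on a back-solved SD, assumed period effects, a paired-difference stand-in for the named ANOVA, and a contrast that period actually affects. The omission itself rests on none of them. It should be corrected, but it does not by itself invalidate the design.

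**What to change.** Analyse the primary AUC and the secondary outcomes with a model that has treatment, period and sequence as fixed effects and participant as a random effect. Add meal-test time, and its interaction with treatment, for the time-course data. Report the period-adjusted sucralose–glucose contrast as the result, and say whether it compares endpoints or within-phase changes.

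The period term uses one degree of freedom. In the simulations it costs about 0.3 to 0.5 points of power when sequences are nearly equal, and about 6 points at 13:6 (80% to 74%), which is the price of removing the bias there. It needs no further participants, visits or samples. Recruitment began in September 2023, and no change to the allocation list is proposed: adjusting it mid-trial in response to the realised imbalance could make later assignments more predictable, and the model change does not depend on it.

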### 2.7. Gut Microbiota Composition

The fecal samples will be collected for gut microbiota analysis before and after each intervention phase. Microbial DNA extraction from fecal samples will be performed using the QIAamp^®^ Fast DNA Stool Mini Kit (QIAGEN, Hilden, GE, USA) (Cat No. 51604) according to the manufacturer’s instructions. DNA concentrations will be measured with the Nanodrop 2000 (Thermo Fisher Scientific, Waltham, MA, USA). The 16S ribosomal RNA (rRNA) gene will be amplified by polymerase chain reaction (PCR). The PCR products will be visualized using agarose gels.

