## 4. Expected Results

The present study will investigate the effects of realistic doses of sucralose (40% ADI) on metabolic markers, appetite, and GM changes in subjects with overweight or obesity. The problem of obesity has spread globally, not just confined to developed countries. Over the past decades, there have been predictions that if the current trend continues, most of the adult population worldwide will be overweight or obese by 2030 [21]. In this context, non-nutritive sweeteners have been implemented to lower calorie consumption and, consequently, mitigate the risk of increased body weight [22]. However, some studies have demonstrated its participation in the development of metabolic alterations.

Some studies have focused on assessing the effects of sucralose on fasting glucose or glycemic and insulinemic responses in animal models [14,23,24,25,26,27] and in healthy or with T1D/T2D subjects [2,6,7,9,13,15,28,29,30,31]. Other studies show evidence of changes in appetite parameters from a single-dose consuming sucralose [10,12,17,32,33,34]. However, the limited evidence evaluating the effects of sucralose consumption on metabolic markers, appetite, and GM in overweight or obese subjects is inconclusive [35,36,37,38]. This study aims to provide crucial information to this population by evaluating some different factors that have been separately studied under varying conditions, mainly in healthy individuals. This planned study has several strengths. First, notably, this is an RCT that will evaluate metabolic markers and appetite associated with GM composition as an explanatory variable in subjects with overweight or obesity. Second, a crossover trial will be used to minimize inter-individual variability since each participant acts as his own control. One advantage of this design is that fewer participants compared to parallel trials are needed to achieve the same level of significance in terms of type I and II errors. Third, this study involves realistic doses of sucralose. Fourth, this is a long-term study, as the interventions will consist of four weeks, separated by a four-week washout period. Overall, the findings of this study will assist health professionals in making more informed recommendations regarding the consumption of commercial sweeteners and food products containing sucralose. 

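### Shannon diversity is to be compared with an independent-groups test although each participant gives four stool samples, so a real microbiota change may be missed

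*Protocol article*

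**What the plan says.** Section 3.6 (Statistical Analysis) plans for alpha diversity that "ANOVA, or the Kruskal–Wallis test, will be used to compare alpha diversity using the Shannon index". For community dissimilarity it names "permutational multivariate analysis of variance (PERMANOVA) on the Bray–Curtis distance" and says nothing about a participant term or how labels are permuted.

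Section 2.7 fixes the sampling: "The fecal samples will be collected for gut microbiota analysis before and after each intervention phase". Section 3.6 agrees: "Four samples per participant will be analyzed: two baselines and two endpoints". Section 4 gives as a strength that "a crossover trial will be used to minimize inter-individual variability since each participant acts as his own control".

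Repeated measures are named in Section 3.6 in one place only, and not for the microbiota: "Time-course data will be analyzed by two-way repeated measures (RM) ANOVA".

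The Introduction lists gut microbiota composition among the further outcomes considered alongside the secondary ones, in terms of change from before to after intervention. The sample size rests on the glycemic AUC; no effect size, variance or power is given for any microbiota measure.

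**The concern.** Kruskal–Wallis is the rank counterpart of one-way ANOVA for independent groups. Four samples from one person are not independent. When the test ignores who gave each sample, stable differences between people count as noise, although they cancel in the comparison of sucralose with control within a person. The usual fear with ignored clustering is false positives. Here it is the reverse: the treatments are compared within person, so the test rejects too rarely.

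A microbiota change is one of the three effects hypothesised in the Abstract, and Section 4 treats microbiota composition as an explanatory variable for the metabolic results. A non-significant result could be read as evidence of no effect when the test had set aside the information that the crossover supplies.

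**Working it through.** **Inputs from the article.** 19 evaluable participants, 80% power and 5% type I error (Section 3.6; two-sided assumed), and four samples per person.

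**The plan's own figure.** There is none for microbiota. The article's inflation for dropout reproduces: 19/(1 − 0.20) = 23.75, rounded up to 24. The 19 cannot be rebuilt because no SD is given. By the noncentral t distribution, a paired comparison with n = 19 has 80% power at a standardised within-person difference of about 0.68; 0.683 was used (power 80.4%). This effect is borrowed from the glycemic sizing only as a yardstick.

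**Assumed.** Within-person correlation ρ, equal for all pairs of samples; normal data; a shift in the sucralose endpoint only.

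**Step 1: why the test is conservative.** Take the two endpoints, with variance σ² each. The true variance of the difference in means is 2σ²(1 − ρ)/n. An independent-groups test uses about 2σ²/n. Its z statistic therefore has SD √(1 − ρ) instead of 1. In the large-sample approximation:

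- type I error = 2[1 − Φ(1.96/√(1 − ρ))]
- power ≈ Φ(0.683√19 − 1.96/√(1 − ρ)) = Φ(2.977 − 1.96/√(1 − ρ))

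| ρ | 1.96/√(1 − ρ) | type I error | power |
|---|---|---|---|
| 0.3 | 2.343 | 1.9% | Φ(0.634) = 74% |
| 0.5 | 2.772 | 0.6% | Φ(0.205) = 58% |
| 0.7 | 3.578 | 0.03% | Φ(−0.601) = 27% |

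Simulated Kruskal–Wallis on the two endpoints gives 68%, 51% and 27%, which fits.

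**Step 2: all four raw sample groups** (simulation, 4,000 runs per setting).

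| ρ | Kruskal–Wallis power | Kruskal–Wallis type I error | Signed-rank on endpoints, power |
|---|---|---|---|
| 0 | 83% | 4.6% | 78% |
| 0.3 | 65% | 1.5% | 78% |
| 0.5 | 42% | 0.2% | 79% |
| 0.7 | 14% | 0.1% | 79% |
| 0.85 | 1% | about 0 | 78% |

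Repeat simulations gave 38% to 44% at ρ = 0.5 and 12% to 14% at 0.7, so the figures are approximate. One-way ANOVA behaves alike: 70%, 46% and 15% at 0.3, 0.5 and 0.7. A paired t test holds about 80% and repeated-measures ANOVA about 85% at every ρ.

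**Step 3: change scores.** Let Y1 to Y4 be the baseline and endpoint of each phase. Under the same model Cov(Y2 − Y1, Y4 − Y3) = σ²(ρ − ρ − ρ + ρ) = 0. The person effect cancels and the two changes are uncorrelated. Kruskal–Wallis then keeps its 5% level, and it and the paired test both have about 51% power.

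**Step 4: PERMANOVA.** Simulated Bray–Curtis data: n = 19, 60 taxa, 199 permutations, 200 runs per setting, four sample groups. The shift equals one within-person SD.

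| Variation between persons | Free permutation rejects | Within-participant permutation rejects |
|---|---|---|
| 35% | 53% | 74% |
| 54% | 6% | 70% |
| 75% | 0.5% | 62% |
| 85% | 0% | 58% |

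With the two endpoints only, the loss starts later: 63% against 73% when 55% of the variation lies between persons, and 17% against 73% at 69%. All these settings are assumptions.

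**The case against.** **PERMANOVA.** A reader might infer that PERMANOVA will be run unblocked, with labels shuffled across people. The article does not say so. It is silent, and a condensed article may leave the permutation scheme to a fuller plan. This objection stands: that part is a request to state the scheme, not an error found.

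**ANOVA.** The ANOVA for alpha diversity carries no label and could be a repeated-measures one. That is possible, but Section 3.6 writes out repeated measures where it means them, and pairing the word with Kruskal–Wallis favours the independent-groups reading. The Kruskal–Wallis branch is unsuitable for raw samples either way.

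**Change scores.** The Introduction speaks of changes from before to after, and on change scores the loss against a paired test disappears (Step 3). This stands as a limit on the point. Section 3.6, however, speaks of analysing four samples, and the article does not settle which quantity enters the test.

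**Size.** A reader might infer that the planned test can hardly detect any effect, or that the trial will wrongly report no change. The documents support neither. They give no within-person correlation, microbiota variance or microbiota effect. At a correlation of 0.3 power is still about 65%, and a false negative presupposes a real effect. The supportable wording is that a real change may be missed.

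**Importance.** Microbiota is not the primary outcome, no power is promised for it, and the error neither creates false positives nor touches the glycemic result. This stands and lowers the severity.

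**Conclusion.** The point holds for alpha diversity. The article names a test for independent groups, describes four repeated samples per person, and relies elsewhere on each person as own control. These do not fit together if raw samples are compared.

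The consequence is a conservative test with reduced power. The reduction is modest at a correlation of 0.3 (about 65% against 78%) and severe from about 0.7 upward (14% or less against about 79%). These figures rest on 19 participants, an assumed standardised paired effect of 0.683, equal correlations and analysis of raw samples. They do not apply to within-phase change scores.

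For PERMANOVA the conclusion is only that the scheme should be stated, because the choice can matter greatly: in the four-group simulation free permutation lost most of its power once about half or more of the variation lay between persons. Severity is moderate, since the outcome is secondary.

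**What to change.** **Shannon index.** Replace the planned test with a within-participant comparison of the sucralose and control phases. One form is a linear mixed model for the phase endpoint with treatment, period, sequence and phase baseline as fixed effects and participant as a random effect. If a rank test is wanted, use a Wilcoxon signed-rank test on the paired endpoints, noting that it does not adjust for period. State which quantity is analysed: endpoints, endpoints adjusted for baseline, or changes.

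**PERMANOVA.** State that the model contains a participant term and that treatment labels are permuted only within participant.

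**Cost.** A change of test and one restriction in the permutation call; no new samples or visits. The Data Availability statement reports no data created or analysed, so the change can still be fixed before results are seen.
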